#### SHI data collection

2.3.2

SHI patient data are transferred for each year for the time period from 01.01.2015 to 31.12.2021; for each patient included, at least one year of baseline data (used to confirm inclusion/exclusion criteria prior to observation period) and at least two years of follow-up data are captured. The data include information on
sociodemographic characteristics (age, gender, and insurance period)outpatient medical care [diagnoses (ICD-10), quarter of diagnoses, procedures, costs of care]pharmaceuticals (dispensed drugs, numbers of packages, prescription date, dispense date, and costs of therapy)medical devices and allied health services (type of therapy or device, service provider, and therapy duration and costs)unemployability (diagnoses, sick leave durations and payments, and durations), andinpatient medical care: main and secondary diagnoses (ICD-10) upon discharge, surgeries and procedures (OPS), date and cause of admission, date and reason for discharge, and DRG code.

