#### SHI study population

2.3.1

The SHI population for EvaClosure is selected from the data pool of a German statutory health insurance fund that comprises over 3 million insured persons. EvaClosure uses data from the years 2015 to 2021. Patients are selected if they
are 18 years or older, andhave a diagnosis code (of the 10th revision of the International Statistical Classification of Diseases and Related Health Problems; ICD-10) for AF documented in at least two different quarters during the baseline period (I48.0, I48.1, I48.2, I48.9)Patients are excluded from the sample in case of
discontinuous data coverage (e.g., due to interrupted insurance periods or change of health insurance fund)an absolute contraindication for ASA (an ICD-10 code for gastric or duodenal ulcers (K25.- or K26.-) or a prescription for methotrexate [Codes within the Anatomical Therapeutic Chemical Classification System (ATC): L01BA01 or L04AX03])previous heart transplant (code within the German Operation and Procedure Classification System; OPS: 5–375)malignant neoplasm of the heart, mediastinum, and pleura (ICD: C38.-) orpregnancy, birth, or postpartum diagnosis in the baseline period (ICD: O–.—)Patients are assigned to the high-risk group if in the baseline period they additionally have the following characteristics:
CHA_2_DS_2_VASc-Score ≥ 2, andhigh risk for bleeding, i.e., if at least one of the following criteria are met:
○HAS-BLED value of ≥ 3, or○an ICD-10 code for other non-traumatic intracranial hemorrhage (I62.-), or○gastrointestinal bleeding (K92.2), or○hematuria (R31), or○bleeding from the respiratory tract (R04.-), or○chronic kidney disease (N18.4)From the high-risk patients, the LAAC intervention group is selected using the following inclusion criteria:
Diagnosis-related group (DRG): F95A (interventional septal occlusion, age < 18 years, or atrial appendage occlusion) andOPS code 8-837.s0 (since 2016) or 8-837.s (before 2016)The control group (best medical care group) is also selected from the group of high-risk patients, defined by the following criteria:

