### Outcome measures and analyses

2.4

The EvaClosure study design consists of four modules that build on one another (see Table 2). For module A1, a cost-of-illness study assesses direct and indirect costs associated with a high risk of stroke and bleeding in patients with AF. Focusing on the high-risk group only, module A2 compares direct and indirect costs associated with LAAC treatment to best medical care. Module B1 quantifies the utility effect of LAAC in terms of QALYs gained compared with standard of care via data of the EvaClosure study population. The subsequent module B2, on the other hand, combines SHI claims data and data from the EvaClosure study population as well as CLOSURE-AF trial results to conduct a cost–utility analysis.

**Table 2 T2:** Overview study modules, design, and outcome measures.

Module	Main Objectives	Study population	Design	Time frame	Costs/Outcomes
A1	To assess cost of illness to high-risk of stroke and bleeding in patients with AF	SHI study population, divided into the high-risk AF group and the AF group without high risk	Longitudinal cohort study, retrospective (difference-in-differences)	2015–2021; 1 year before and 4 years after inclusion per individual	direct and indirect costs
A2	To assess direct and indirect costs of LAAC intervention vs. best available medical care in high-risk patients with AF	EvaClosure study population: high-risk AF patients divided into intervention and control groups as per the CLOSURE-AF protocol.	Longitudinal cohort study, prospective (difference-in-differences)	2018–2025; enrollment starting in 01/2021 with a follow-up of up to 24 months	Direct and indirect costs
		SHI study population: the high-risk AF group divided into intervention and control groups as close as possible to the CLOSURE-AF protocol	Longitudinal cohort study, retrospective (difference-in-differences)	2015–2021; 1 year before and 4 years after inclusion per individual	
B1	To assess the utility effect of LAAC compared with best medical care	EvaClosure study population: high-risk AF patients divided into intervention and control groups as per the CLOSURE-AF protocol	Longitudinal cohort study, prospective	2018–2025; CLOSURE-AF enrollment starting in 03/2018; obtaining informed consent for prospective and retrospective participation in EvaClosure started in 01/2021, patient individual follow-up of up to 24 months	Health-related quality of life, QALYs

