#### B2: health economic evaluation of LAAC

2.4.4

In module B2, a cost–utility analysis compares LAAC with best medical care. Based on the results of modules A2 and B1, the ICER up to five years after intervention is calculated, with QALYs serving as the main effect measure. The ICER determines the costs to SHI (perspective 1) as well as society (perspective 2) for an additional QALY gained. Depending on the underlying perspective, it will be calculated from direct and indirect costs in SHI claims data, supplemented by an analysis of FIMA data from EvaClosure study patients and QALYs derived from EvaClosure study patients as described in the previous section.

A Markov model adapted from the literature (46) will be employed to capture a lifetime horizon to assess long-term effects on costs and health-related quality of life. The transitions between different health states are linked by probabilities, and the Markov property assumes that the transition probabilities result exclusively from the current state (not from history). The parameters of the initial model (46) will be fine-tuned by SHI claims data estimates to capture probabilities for patients with high-risk AF, with risk estimates evaluated among matched populations of both treatment and control claims data groups. Further relevant parameters depending on the underlying Markov state (costs, utilities) will be derived from SHI claims data analyses and the EvaClosure primary data. Parameters that cannot be sufficiently quantified by one of these data sources may be extracted from the literature or health states may be coarsened. After completion of the CLOSURE-AF trial, clinical study results and comorbidity data of EvaClosure-enrolled patients will be used to adjust the final model.

To compare costs and health effects in different years, future costs and benefits will be discounted by an annual discount rate of 3% for SHI expenditures, indirect costs, and QALYs (47). The influence on the results will be systematically addressed in sensitivity analyses as described in the next section.

Figure 1 provides an overview of the study design, the main analyses, the two corresponding data sources, and matching criteria to ensure comparability of the SHI- and trial samples.

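### As worded, the SHI cohort needs two years of captured follow-up with no exemption for death, which understates claims-based mortality risk and biases costs in an undetermined direction

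*Protocol article*

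**What the plan says.** Section 2.3.2 (SHI data collection) describes yearly data transfers for 01.01.2015 to 31.12.2021. It states "for each patient included, at least one year of baseline data", used to confirm eligibility, "and at least two years of follow-up data are captured". Section 2.3.1 (SHI study population) lists among the exclusions "discontinuous data coverage (e.g., due to interrupted insurance periods or change of health insurance fund"; death is neither named nor exempted. Table 2 gives the SHI time frame for modules A1 and A2 as "1 year before and 4 years after inclusion per individual". The article does not say what ends a patient's follow-up.

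These data have two uses. Section 2.4.2 estimates the cost difference between LAAC and control over two and five years. Section 2.4.4 tunes the parameters of a literature-based Markov model, "with risk estimates evaluated among matched populations of both treatment and control claims data groups".

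For the LAAC group, section 2.3.1 requires DRG "F95A (interventional septal occlusion, age < 18 years, or atrial appendage occlusion") together with OPS code 8-837.s0 (8-837.s before 2016). The control group must have no LAAC documented. There the same DRG and OPS codes stand side by side, separated by a semicolon, without saying whether one or both are needed to exclude a patient.

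**The concern.** Entry to a cohort should depend only on what is known up to the index date. The baseline year meets that test; a requirement for two years of captured data after index does not. A patient who dies six months after LAAC, or six months after starting an anticoagulant, cannot supply two years of data, so a programmer following the text would leave that patient out.

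The affected outcomes are central to the evaluation. Section 2.4.3 intends to credit QALYs from reduced mortality, and fatal strokes and bleeds are among the events that LAAC is meant to change. If early deaths are missing from the claims cohort, the risk estimates from it describe survivors, and the cost estimates omit end-of-life care. Matching on baseline characteristics cannot undo selection on something that happens after baseline.

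The LAAC definition raises a smaller question. The OPS code identifies the procedure, so adding a DRG condition can only shrink the group. A patient with the OPS code but another DRG leaves the LAAC group and, depending on how the control rule is read, may be lost altogether or counted as a control.

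**Working it through.** The article states no figure for the effect of these rules, so there is nothing to reproduce. The figures below rest on assumed inputs.

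**1. What the data window allows.** Data run from 01.01.2015 to 31.12.2021. With one baseline year, the earliest index date is the start of 2016. With two years of potential follow-up, the latest is the end of 2019. A rule on potential follow-up is therefore feasible and would not need survival as a condition.

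**2. Share removed under the literal rule.** For annual mortality m, the share dying within two years is D = 1 − (1 − m)².

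- m = 8%: 1 − 0.92² = 15.4%
- m = 10%: 1 − 0.90² = 19.0%
- m = 15%: 1 − 0.85² = 27.8%
- Wider range: m = 3% gives 5.9% and m = 20% gives 36.0%

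Under the literal rule, two-year mortality in the retained SHI sample is 0% whatever m is.

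**3. Effect on mean cost.** Let survivors cost 1 unit per year, so 2 units over two years. Let those who die live one year on average, at k times the survivors' annual cost. The full-cohort mean is 2(1 − D) + Dk, and the survivor-only mean is 2. The error in total cost is 2 / [2(1 − D) + Dk] − 1. Per person-year alive, the full-cohort rate is [2(1 − D) + Dk] / [2(1 − D) + D], against 1 for survivors. At m = 10% (D = 0.19):

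| k | Error in two-year total cost | Error in cost per person-year alive |
|---|---|---|
| 1 | 2/1.81 − 1 = +10.5% | 0% |
| 1.5 | 2/1.905 − 1 = +5.0% | −5.0% |
| 2 | 2/2.00 − 1 = 0% | −9.5% |
| 3 | 2/2.19 − 1 = −8.7% | −17.4% |
| 5 | 2/2.57 − 1 = −22.2% | −29.6% |

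Total cost is understated only if k exceeds 2. Cost per person-year is understated for any k above 1.

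**4. Effect on the LAAC-minus-control difference.** Take assumed annual mortality of 8% with LAAC and 12% with control, and equal survivor costs. Then D = 15.36% and 22.56%. The survivor-only difference is 2 − 2 = 0. In the full cohort:

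- k = 3: (1.6928 + 0.4608) − (1.5488 + 0.6768) = 2.1536 − 2.2256 = −0.072
- k = 1: (1.6928 + 0.1536) − (1.5488 + 0.2256) = 1.8464 − 1.7744 = +0.072

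The same exclusion hides a saving in one case and an extra cost in the other.

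**5. DRG condition.** If a share s of LAAC stays falls outside F95A at r times the cost of the others, the mean stay cost is off by 1 / [(1 − s) + sr] − 1. With r = 2, s = 2%, 5% and 10% give −2.0%, −4.8% and −9.1%. With r = 1 the error is zero. The document gives neither s nor r.

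**The case against.** The strongest reply is that the two-year sentence stands in the data collection section, not among the eligibility criteria, and may mean only that the data window leaves two years after index. The examples given for discontinuous coverage are administrative, and a condensed article may leave the handling of death to the full protocol. That reading is possible. However, the sentence speaks of data captured for each included patient and puts the two years in parallel with a baseline year that really is required. Nothing in the article points to potential follow-up instead.

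A second reply is that the Markov model does not rest on SHI data alone. Section 2.4.4 starts from a literature model, allows literature values where the data are insufficient, and adjusts the final model with CLOSURE-AF results. Section 2.5 adds probabilistic, scenario and trial-based sensitivity analyses. This stands in part. A reader might infer that the model's two-year mortality becomes zero, but the article does not say that mortality transitions come from the claims cohort. These steps still do not restore the claims costs of patients who died. The probabilistic analysis addresses parameter uncertainty, not selection, and the trial-based one is aimed at the selection of the EvaClosure sample.

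Two further inferences are tempting and not supported. One is that costs are simply too low: survivors accrue two full years of cost while those who die stop accruing, so the sign depends on a cost ratio that the article does not give. The other is that the DRG condition removes complicated LAAC stays. That depends on grouping rules outside the document. Section 2.4.2 also plans to verify matching against periprocedural and adverse events, which might reveal a shortfall.

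**Conclusion.** The concern holds for the text as written. Requiring two years of captured follow-up with no exemption for death conditions both SHI groups on a post-index outcome. Mortality and fatal-event risks taken from these data are understated. The two- and five-year costs, the incremental cost and the ICER are biased in a direction that the document does not determine.

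At an assumed annual mortality of 8-15%, 15-28% of eligible patients would be removed. At 10%, the survivor-only two-year mean cost could be off by anything from +10.5% to −22.2% as the cost ratio k goes from 1 to 5. Both ranges rest on assumed inputs, and the cost range also assumes one year of life on average among those who die. If only potential follow-up is intended, the selection does not arise, but the text must then say so. Because the rule sits upstream of modules A1, A2 and B2, it should be settled before the cohort is built.

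The LAAC definition is a lesser point. The double condition can only remove OPS-coded patients, and the control exclusion is ambiguous. Whether those patients are the complicated or costly ones has to be checked in the extract.

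**What to change.** Replace the follow-up sentence with a rule that does not depend on survival:

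- Require an index date that allows two years of potential follow-up, and continuous coverage in the baseline year.
- Follow each patient to death, fund exit or 31.12.2021, whichever comes first.
- Keep patients who die, with their costs to death. Death is not discontinuous coverage.
- Treat fund exit as censoring with a suitable method, for example inverse-probability-weighted costs. Beyond two years the same method must cover administrative censoring: patients indexed in 2018 or 2019 cannot reach the four years after inclusion given in Table 2.

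For the LAAC group, identify the procedure by OPS code 8-837.s0 or 8-837.s, exclude any patient with that code from the control group, and report the number and cost of OPS-coded stays outside F95A.

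The cost is small: a changed cohort definition and a censoring-adjusted cost estimate. The listed data include insurance period, hospital discharge date and reason, OPS and DRG, so little or no new data should be needed. Because a date of death is not among the listed items, the sponsor should confirm that death outside hospital can be told apart from fund exit. The downside is a more heterogeneous LAAC group and some extra analysis work.

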### Outcome measures and analyses

2.4

The EvaClosure study design consists of four modules that build on one another (see Table 2). For module A1, a cost-of-illness study assesses direct and indirect costs associated with a high risk of stroke and bleeding in patients with AF. Focusing on the high-risk group only, module A2 compares direct and indirect costs associated with LAAC treatment to best medical care. Module B1 quantifies the utility effect of LAAC in terms of QALYs gained compared with standard of care via data of the EvaClosure study population. The subsequent module B2, on the other hand, combines SHI claims data and data from the EvaClosure study population as well as CLOSURE-AF trial results to conduct a cost–utility analysis.

**Table 2 T2:** Overview study modules, design, and outcome measures.

Module	Main Objectives	Study population	Design	Time frame	Costs/Outcomes
A1	To assess cost of illness to high-risk of stroke and bleeding in patients with AF	SHI study population, divided into the high-risk AF group and the AF group without high risk	Longitudinal cohort study, retrospective (difference-in-differences)	2015–2021; 1 year before and 4 years after inclusion per individual	direct and indirect costs
A2	To assess direct and indirect costs of LAAC intervention vs. best available medical care in high-risk patients with AF	EvaClosure study population: high-risk AF patients divided into intervention and control groups as per the CLOSURE-AF protocol.	Longitudinal cohort study, prospective (difference-in-differences)	2018–2025; enrollment starting in 01/2021 with a follow-up of up to 24 months	Direct and indirect costs
		SHI study population: the high-risk AF group divided into intervention and control groups as close as possible to the CLOSURE-AF protocol	Longitudinal cohort study, retrospective (difference-in-differences)	2015–2021; 1 year before and 4 years after inclusion per individual	
B1	To assess the utility effect of LAAC compared with best medical care	EvaClosure study population: high-risk AF patients divided into intervention and control groups as per the CLOSURE-AF protocol	Longitudinal cohort study, prospective	2018–2025; CLOSURE-AF enrollment starting in 03/2018; obtaining informed consent for prospective and retrospective participation in EvaClosure started in 01/2021, patient individual follow-up of up to 24 months	Health-related quality of life, QALYs
B2	Health economic evaluation of LAAC intervention	EvaClosure study population and SHI study population (cf. module A2)	Cost–utility analysis; Difference-in-differences; Markov model	2 years, 5 years, lifetime horizon	ICER
		CLOSURE-AF trial results			

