#### A1: resource utilization and cost of illness associated with high risk of stroke and bleeding in patients with AF

2.4.1

In the SHI patient database, ICD-10 diagnostic codes will be used to select high-risk AF patients from AF patients without high risk of bleeding and stroke for the cost analysis in module A1 (see section “SHI study population”). A patient's index quarter, regardless of later being allocated to the high-risk group or not, will be the quarter in which the SHI patient inclusion criteria are fulfilled for the first time in the pre-observation year. In addition to these criteria (also using ICD-10 diagnosis codes^6^), patients will be allocated to the high risk of bleeding and stroke group if they have a CHA_2_DS_2_VASc-Score ≥ 2 and one of the following: a HAS-BLED value of ≥3, a diagnostic code for other non-traumatic intracranial hemorrhage, gastrointestinal bleeding, hematuria, bleeding from the respiratory tract, or chronic kidney disease in the observation period. Applicable ICD-10 codes to assess these indications were selected in cooperation with the CLOSURE-AF investigators.

Hierarchically regularized entropy balancing (39, 40), a method for statistical matching, will be used to ensure similar characteristics in terms of age, gender, morbidity (Charlson comorbidity index), and healthcare costs between the high-risk group and the control group without the high risk at baseline.

The two patient groups will be descriptively characterized; location and dispersion measures will be compared with respect to the distribution of appropriate metric variables such as age, morbidity indices, and bleeding risk. Frequencies will be reported for ordinal variables. Differences in mean values for dependent variables, such as resource utilization and direct and indirect costs, will be analyzed by performing a bilateral significance test of independent samples depending on the specific variable distribution in the actual data. The analysis will be conducted by a difference-in-difference design, carried out as two-way fixed effects regression model, alleviating further unobserved structural differences between both groups that may remain after balancing.

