#### A2: direct and indirect costs in high-risk AF patients: LAAC procedure vs. best available medical care

2.4.2

To estimate direct and indirect costs, a population with maximum similarity to the EvaClosure study population will be selected from SHI claims data by statistical matching. Age, gender, comorbidity, CHA_2_DS_2_VASc and HAS-BLED scores, and medications (by classification) taken by control group patients will be used for matching of the populations, as observed by the quarter and year in which they and their statistical match meet the inclusion criteria. Matching will be verified using clinical trial data on medication, periprocedural events, (serious) adverse events, and comorbidities detected during follow-up visits of CLOSURE-AF trial patients. In the SHI population, healthcare costs of the LAAC group within a 2- and 5-year time frame will be estimated as the difference between the costs induced by the intervention group and the control group. Indirect costs will be evaluated based on the difference in the average length of incapacity to work documented per group, priced using industry-specific average employee compensation in Germany.

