Because patients are surveyed with the FIMA every six months, questions on resource utilization covering a period of 12 months (see above) were modified to cover a period of six months.Information on sociodemographic and socioeconomic data as well as on drug utilization is collected in the CLOSURE-AF study. Therefore, questions covering these topics (e.g., on sex, age, marital status, and drug utilization within the last seven days) were waived.To estimate the indirect costs, two questions on unemployability (i.e., duration within the last six months and profession) were added.Using descriptive statistics, measures of location and dispersion will be compared for similarity. Difference-in-differences estimation will be applied to evaluate the incremental costs of the LAAC procedure by comparing the costs of services incurred by the intervention group and the control group. The time frame covers five years, comparing the average costs of both groups before and after the quarter of LAAC or first treatment with one of the pharmaceuticals defined as best medical treatment in the study design section.

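### Table 2 gives claims patients four years of follow-up each, but the two-year minimum in the data-collection section admits patients who cannot have it

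*Protocol article*

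**What the plan says.** Four places in the protocol article bear on how long each claims patient is followed.

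- **Table 2, SHI rows of modules A1 and A2:** "2015–2021; 1 year before and 4 years after inclusion per individual".
- **SHI data collection (2.3.2), data window:** "SHI patient data are transferred for each year for the time period from 01.01.2015 to 31.12.2021".
- **SHI data collection (2.3.2), minimum per patient:** "for each patient included, at least one year of baseline data", and "at least two years of follow-up data are captured".
- **Module A2 (2.4.2):** "healthcare costs of the LAAC group within a 2- and 5-year time frame will be estimated". The estimation is described thus: "The time frame covers five years, comparing the average costs of both groups before and after the quarter of LAAC or first treatment".

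The only coverage rule in the SHI study population section (2.3.1) excludes "discontinuous data coverage (e.g., due to interrupted insurance periods or change of health insurance fund"). Its examples concern a patient leaving the fund or interrupting insurance, not the end of the data window. No section limits index dates to 2016–2017.

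**The concern.** Table 2 and the data-collection section describe different cohorts. Table 2, read as written, describes patients who all have four years after inclusion. The minimum in 2.3.2 describes patients who have two or more. Within a window that ends on 31.12.2021, patients who enter in 2018 or 2019 satisfy the second description and cannot satisfy the first.

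This goes beyond wording because of the cost profile the authors expect. The Discussion anticipates that the one-time procedure cost is offset over the following years by lower drug spending and fewer complications. Cost in the LAAC group is therefore concentrated at index, and the hoped-for savings come later. If some patients are observed for two years and others for four, one post-index average gives the early quarters more weight than a true four-year cost would. If LAAC and control patients are indexed at different calendar times, the truncation also differs between the groups. Module B2 takes the A2 cost difference into the ICER.

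**Working it through.** **Inputs from the document**

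- Data window (2.3.2): 01.01.2015 to 31.12.2021, which is 7 years or 28 quarters.
- Minimum baseline (2.3.2): 1 year.
- Minimum follow-up (2.3.2): 2 years.
- Follow-up in Table 2: 4 years.
- Distribution of index dates: not given, so assumed below.

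**Step 1. Index dates that each rule allows**

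- Earliest index: 01.01.2015 + 1 year = 01.01.2016.
- Latest index under the two-year minimum: two years before the end of the data = 31.12.2019.
- Latest index with four full years: four years before the end of the data = 31.12.2017.

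Counted in quarters, with the index quarter itself not counted as follow-up, the two-year minimum admits 2016Q1 to 2019Q4 (16 quarters). Four full years are available only for 2016Q1 to 2017Q4 (8 quarters). Table 2's four years for each individual is therefore not reproduced by the admission rule in 2.3.2. It would be reproduced if indexing stopped at the end of 2017, which no section says.

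**Step 2. Share of A2 patients with less than four years**

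Share = weight of admissible index quarters after the last complete one ÷ weight of all admissible quarters. With even entry this is 8/16 = 50%. If the index quarter counts as follow-up, one more quarter qualifies under each rule, and the share is 8/17 = 47%.

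| Assumed index dates | Share with less than 4 years |
|---|---|
| Even | 47–50% |
| Growing 10% a year | 52–55% |
| Growing 20% a year | 57–59% |
| Growing 40% a year | 64–66% |
| Falling 20% a year | 36–39% |
| Half in 2016, the other half even over all admissible quarters | 24–25% |

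The range is about 24% to 66%. It applies to A2, where the index is the quarter of LAAC or of first treatment. It does not carry over to A1, where the index is "the quarter in which the SHI patient inclusion criteria are fulfilled for the first time in the pre-observation year".

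**Step 3. Illustration of what unequal follow-up can do**

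Let t be the index time in years from 01.01.2016, with t from 0 to 4. Observed follow-up, capped at four years, is min(4, 6 − t).

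- Even entry: half the patients have 4 years. The other half have 2 to 4 years, with mean 3. Mean follow-up = 0.5 × 4 + 0.5 × 3 = 3.5 years.
- A raw mean of accumulated cost then covers 3.5/4 = 87.5% of the four-year window.
- An annual cost from pooled person-time, scaled to four years, counts a one-off cost at index 4/3.5 = 1.14 times.
- An average of patient-level annual costs, scaled in the same way, counts it 0.5 + ln 2 = 1.19 times.

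With entry growing 20% a year, mean follow-up is 3.37 years and the two factors are 1.19 and 1.25. With entry falling 40% a year, 27% fall short, mean follow-up is 3.78 years and the factors are 1.06 and 1.08. These factors belong to an annualised cost rescaled to four years, which the article does not say it will use. They show scale only.

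**The case against.** The strongest reply is that the two statements need not clash. Two years is a floor for data collection, four years is the analysis frame, and a patient with four years meets both. The five-year frame in 2.4.2 is then one year before plus four after, which agrees with Table 2. On this reading nobody indexed after 2017 enters the analysis. That is possible, but nothing in the article limits indexing that way, and a floor of two years has little purpose if four are required.

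A variant is that four years is the maximum window. Table 2 tells against this: for the trial population it marks the 24 months explicitly as an upper limit, while the SHI rows carry no such qualifier and refer to each individual. If a maximum was meant, the entry still needs correcting.

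Three parts of the reply stand.

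- A reader might infer that truncated patients will simply be averaged in with no rule to handle them. The article does not establish this. It is a condensed account, and the handling of administrative censoring may be in an analysis plan that is not shown. The stated method is difference-in-differences, specified for A1 as a two-way fixed effects regression, and such a model can run on unequal follow-up. Running on it does not by itself turn a single post-index effect into a four-year cost, however.
- A reader might take half as the affected share. That holds only for index dates spread evenly over 2016 to 2019.
- A 2-year cost estimate is already planned, and every patient who meets the minimum in 2.3.2 has complete data for it.

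**Conclusion.** The inconsistency holds. The four years in Table 2 and the two-year minimum in 2.3.2 cannot both decide who enters the claims analysis, and the latest index date differs by two years between them (31.12.2017 against 31.12.2019). This follows from the document's own dates and needs no assumption.

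The consequence is conditional. If the two-year minimum operates, A2 patients indexed in 2018 and 2019 are administratively censored before year 4: 50% under even entry, roughly 24% to 66% under the other patterns tried. A single before/after average would then over-weight early quarters, including the LAAC procedure, and would not be a four-year cost. How far, and in which direction, this moves the cost difference and the ICER cannot be fixed from the article. It depends on the estimator and on whether LAAC and control index dates are distributed differently, and the article gives no index dates for either group. The 2-year cost difference is not affected.

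**What to change.** First, settle the rule and say so in one place. Either restate the SHI rows of Table 2 as *1 year before and 2 to 4 years after inclusion, depending on index date*, or keep the four years and restrict indexing to 2016–2017 in 2.3.2.

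If the two-year minimum is kept:

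- Use all index years, 2016–2019, for the 2-year cost difference already planned.
- Estimate costs beyond two years in one of two ways: in patients indexed in 2016–2017 only, or as cumulative cost by quarter since index, with adjustment for administrative censoring at 31.12.2021.
- Report the number of patients still observed, per group, at each year since index.

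The cost is a few lines in Table 2 and sections 2.3.2 and 2.4.2, and modest programming on data already held. The drawback is that estimates for years 3 and 4 rest on fewer patients and will have wider intervals. Restricting all indexing to 2016–2017 would also take the later entrants out of the 2-year estimate, so the first option makes better use of the data.
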